#### *Inter-rater reliability*

Research assistants have been trained in Structured Clinical Interview for DSM-5 (SCID) and in carrying out clinical assessments by the University of Manchester for a previous grant funded study. Inter-rater reliability will be measured using calculations of the Kappa statistic [34] assessed during investigator meeting rating precision exercises.

#### *Statistical Analysis*

Initial descriptive analysis will be conducted to study the profile of the subjects and investigate group differences at baseline on main demographics and clinical measures. Frequencies and proportions will be used for categorical variables and mean and standard deviations, median and inter-quartile range, minimum and maximum for continuous variables. No statistical significance tests will be used to compare groups. Drop out, visit frequency and adherence to treatment will be summarized by group with the appropriate descriptive statistics.

The main analysis will follow the Intention-to-treat (ITT) principle in which subjects are assigned to treatment groups as randomized. Subjects that drop out of the study will be included in the analysis provided that they have a baseline score for the outcome. For the primary hypothesis, the MADRS scores at week 12 will be compared between groups using a mixed effect model. The outcome for the model will be all post-baseline MADRS scores and the fixed effects will include baseline MADRS scores, treatment group, time (post-baseline timepoints) and a treatment group by timepoint interaction. To account for the dependencies between repeated measures on the same patients, an intercept for each individual will be included as a random effect. A linear contrast will be used to test the primary hypothesis, the difference between groups in at week 12 in MADRS scores. Given the modest sample size it will likely not be possible to use as random slope for each subject, however the covariance matrix of the residuals of the model can be allowed to correlate to account for dependencies across time. Two tailed tests and an alpha level of 0.05 will be used for significance. All estimates will be presented with the 95% confidence interval. To give an estimate of effect size, standardized regression coefficients will be calculated using the overall SD of the baseline outcome scores as the metric. One advantage of this approach is it gives the magnitude and direction of effect in units of patient population of interest.

275

276 Secondary analyses will use similar mixed models to that of the primary outcome, baseline  
277 adjusted with time, treatment group and the interaction between treatment group and time as  
278 independent variables. As for the primary outcome, the main timepoint of interest is 12 week  
279 follow up and treatment effects will be determined by contrasts at the measured timepoint.  
280 To compare response and remission rates between groups logistic regression will be used in  
281 which patients will be classified as in remission or not according to standard criteria on the  
282 MADRS scale. As there are multiple measures, p values will be adjusted for multiple  
283 comparisons using a correction based on controlling the family-wise error. Outcomes at  
284 timepoints other than 12 week follow-up will be considered exploratory and the main focus  
285 will be effect sizes (standardized regression coefficients).

286

287 To compare frequency of adverse events descriptive summaries will be presented by  
288 treatment group. Differences in the rates of AEs will be assessed by generalized linear mixed  
289 model with Poission or negative binomial distribution will be used given sufficient numbers  
290 of events, where time, treatment group and their interaction are fixed effects with subjects as  
291 random effects. Alternatively, simple count models will be used at each timepoint given the  
292 limited sample size and complexity of GLMM models.

293

294 It is likely there will be some drop-out of participants from the trial. Baseline predictors of  
295 missingness can be identified using logistic regression with the outcome (missing or not).  
296 Mixed effect models fitted through maximum likelihood can use all available information in  
297 the data potentially avoiding removal of dropout subjects from the analysis. Moreover, by  
298 including baseline predictors of missingness in the statistical models, the analysis may

assume the data to be missing at random (MAR). Diagnostic analysis will be conducted through checking residuals for outliers, influential data points and normality. If outliers or influential points are found a sensitivity analysis will be conducted after removing such points to see if the main findings change.

The exploratory hypothesis that baseline lipid/CRP levels will affect response to simvastatin will be tested by adding the baseline lipid/CRP to a model for the primary outcome at 12 weeks, adjusted for baseline and including a treatment group by baseline lipid/CRP. The lipid/CRP level will be considered moderators if interaction with treatment group is significant (at significance level of 0.05, using bootstrapping for inference and construction of confidence intervals). If this is the case, exploratory plots that look at the group effect at different levels of the moderators will be used to study the nature of the moderation.

In order to test the hypothesis that changes in peripheral levels of lipids/CRP will be a mediator in the path between treatment and change in MADRS scores, an initial descriptive analysis will be conducted to look at the bivariate association between treatment group and change in lipid/CRP levels, and between change in lipid/CRP (at 4 and 12 weeks) and change in MADRS scores. A mediation model will then be fitted to the data that joint models the effects of treatment on the change in lipid/CRP at 4 weeks and MADRS at 12 weeks. The mediation effect is tested by the proportion of the total effect from treatment group to change in MADRS that goes through change in lipid/CRP. This model will be fitted in Lavaan in R or Mplus 7.11[35] and the indirect effect estimated through bootstrap resampling. Given the sample size, note the effect sizes for the indirect mediation pathway would need to be relatively large [36].

323

324 *Safety Monitoring*

325 Adverse events monitoring from the time informed consent is obtained until follow-up at 12  
326 weeks (using the side effect assessment scale). Laboratory parameters including total serum  
327 cholesterol, LDL, HDL, triglyceride, AST, ALT, LDH and CPK will be checked by the study  
328 physician before patient entry into the trial, and if there are any safety issues for which the  
329 patient should not be started on study medication, he/she will not be included to the study.

330

331 *Study coordination*

332 Local investigators will chair a weekly meeting with research assistants to help coordinate the  
333 study. The chief investigator will hold meetings with the research team every two weeks via  
334 Skype.

335

336 *Data protection and confidentiality*

337 For data security, consent forms and paper copies of assessment tools having any identifying  
338 information such as name, address or phone number of participants will all be stored in  
339 locked filing cabinets in a secure office. All computerised data will be encrypted and  
340 password protected. We will also maintain quarterly site audits of the data and security  
341 protocols across each site. These audits will be independent from the investigators and the  
342 sponsor.

343

344 *Trial Steering Committee (TSC)*

The responsibility of TSC will be to offer the overall supervision and monitoring of conduct of the trial. The TSC will be independent of the investigators, their employing bodies, funders and sponsors. The TSC will monitor overall trial progress, conduct and will also advise on scientific credibility. The TSC will reflect and act, as suitable, upon the recommendations of the Data Safety and Monitoring Board (DSMB) for deciding if the trial needs to be stopped on grounds of safety or efficacy.

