45 paralysis, fatigue and interpersonal sensitivity [15, 16]. Hence lipid-lowering effects of statins  
46 may also play a role in putative antidepressant effects of this class of drugs. Data from the  
47 STAR\*D trial indicate poorer treatment response to SSRIs in those with atypical depression  
48 and therefore, statins could provide genuinely novel therapeutic targets for this group of  
49 people with TRD [17].

50

51 We plan to carry out an RCT involving 150 participants with treatment-resistant depression,  
52 with the aim of determining whether the addition of simvastatin (20mg daily), a lipophilic  
53 statin that readily crosses the blood-brain barrier [18, 19], to treatment as usual (TAU) for 12  
54 weeks leads to a reduction in depressive symptoms compared with placebo added to TAU.  
55 We predict that treatment-resistant depression patients will show improvement in mood with  
56 simvastatin treatment and that the response will be associated with reduction in lipid  
57 biomarkers (i.e. plasma LDL and LDL/HDL ratio). A secondary hypothesis relates to  
58 simvastatin's effects on putative inflammatory biomarkers. High LDL and low HDL  
59 contribute substantially to immunological up-regulation in the development of  
60 atherosclerosis. Pro-inflammatory cytokine (Interleukin-6 and Tumour Necrosis Factor)  
61 levels are often altered in depressed patients and decreased by successful antidepressant  
62 therapy [20, 21]. We therefore predict that in those treatment-resistant depression patients  
63 who show improvement in mood with simvastatin treatment, that response will be associated  
64 with reduction in inflammatory biomarkers. Our mechanistic hypothesis is that the anti-  
65 inflammatory and lipid-reducing effects of simvastatin will improve neuroinflammation and  
66 thus mediate a response to simvastatin.

67   **Methods**

68   A pragmatic multi-centre, 12-week, double blind, placebo controlled randomised trial of  
69   simvastatin added to treatment as usual (TAU) for patients suffering from a DSM-5 major  
70   depressive episode that has failed to respond to at least two trials of antidepressants. This will  
71   be a parallel group study with 75 participants in each arm. Recruitment will occur at  
72   outpatient psychiatric clinics in Karachi, Lahore, Hyderabad, Rawalpindi and Quetta  
73   Pakistan. Consistency of procedures across sites will be ensured through vigorous training  

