#### 95 *Sample Size*

96 We estimate a moderate effect size of 0.60 will be reported at week 12. Assuming a type-1  
97 error of 5%, we will need to follow up 120 patients across the two groups to achieve 90%  
98 power at Week 12. With an anticipated dropout rate of 20% by Week 12, we will randomise  
99 150 participants. An effect size of 0.4 or greater for difference in MADRS scores in  
100 randomised controlled trials of antidepressants versus placebo has been suggested as  
101 necessary to suggest clinical utility for an antidepressant used as monotherapy. A sample of  
102 120 participants is therefore powered to detect moderate to large effect sizes and trends  
103 towards significance in areas of smaller effect.

104

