#### *Randomisation and Allocation Concealment*

Randomisation service will be provided by an independent statistical support service based in the UK. We will stratify randomization based on severity of depressive symptoms at baseline and study centre. Participants will be assigned to groups via random generation of allocation sequence, balanced across allocation group. Each participant will be assigned a unique study patient identification number once they have given informed consent and eligibility has been confirmed. The central trial pharmacist will prepare a 12-week package of treatment bearing the patient's name and ID number and send it to the site pharmacy. Thus, the site pharmacy will not know the treatment allocated to the patient. A study information leaflet will be given

to the participant, explaining that they are in a clinical trial and that in addition to TAU they are taking a placebo or simvastatin. This leaflet will also have the name of the local PI's.

Allocation will be masked from study investigators and co-investigators until participants have completed all follow-ups and the database is cleaned and locked. The trial pharmacist at the central pharmacy will keep the drug codes. There will be detailed protocols regarding maintenance of blindness for raters and governing unblinding procedures in case of emergency for pharmacists. To assess the integrity of blinding procedures, participants and independent raters will be asked to complete a conventional guess form asking whether they believe participants received simvastatin or placebo as a treatment after the final ratings have been completed.

If any participant develops side effects or suffers an emergency requiring drug unblinding, the responsible consultant and care team will be informed of the trial drug, probable side-effects and make a decision of participant continuation in the trial. Participant well being and safety will be crucial at all times and locally and internationally accepted Good Clinical Practice will be observed across the trial's governance procedures

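### Randomisation is stratified by study centre, but the primary model has no centre term; if centres differ, the analysis is mildly conservative

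*Protocol*

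**What the plan says.** The protocol's Randomisation and Allocation Concealment section states: "We will stratify randomization based on severity of depressive symptoms at baseline and study centre". The Methods section places recruitment at "outpatient psychiatric clinics in Karachi, Lahore, Hyderabad, Rawalpindi and Quetta", taken here as five centres.

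The Statistical Analysis section then writes out the primary model. The outcome is every post-baseline MADRS score, and "the fixed effects will include baseline MADRS scores, treatment group, time (post-baseline timepoints) and a treatment group by timepoint interaction". For the repeated measures, "an intercept for each individual will be included as a random effect". The primary test is a contrast between arms at week 12, and "Two tailed tests and an alpha level of 0.05 will be used for significance".

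The secondary mixed models take the same form, with baseline, time, group and group by time. Centre is not named in any of these models. The same section allows baseline predictors of missingness to be added, but does not name centre among them.

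**The concern.** Stratifying by centre balances the arms within each centre, so differences between centres largely cancel out of the treatment contrast. A model without centre does not know this and still counts those differences as error. The participant intercept does not help: centre differences are absorbed into the between-participant variance, which is part of what sets the standard error of the week-12 contrast.

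Wherever centres differ after baseline adjustment, the reported standard error therefore exceeds the true one, the interval is wider than it need be, and the test rejects less often than its nominal 5%. At stake is efficiency that the stratified design makes available and the analysis would not use. This matters more at smaller effects. The Sample Size section names 0.4 as the level suggesting clinical utility for an antidepressant used alone, while powering the trial for 0.60.

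**Working it through.** **Inputs from the protocol.** Effect size 0.60 ("We estimate a moderate effect size of 0.60 will be reported at week 12"); two-sided alpha 0.05; 120 evaluable participants, so 60 per arm; power 90%; dropout 20%; 150 randomised 1:1. The effect size 0.4 is also from the Sample Size section.

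**Input assumed.** ρ, the share of week-12 outcome variance (given baseline) that lies between centres. The protocol gives no figure. The range shown is 0 to 15%.

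**The plan's own figure.** n per arm = 2 × (1.96 + 1.2816)² / 0.60² = 58.4, so 59 per arm and 118 in total, against 120 stated. With 60 per arm the power is Φ(0.60 × √30 − 1.96) = Φ(1.326) = 90.8% (90.3% by noncentral t). 120 / 0.8 = 150. The sample size reproduces.

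**Effect of omitting centre.** Take total residual SD as 1 and arms balanced within centre.

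- Reported SE = √(2/60) = 0.1826; true SE = 0.1826 × √(1 − ρ).
- Actual type I error = 2 × [1 − Φ(1.96 / √(1 − ρ))].
- Power without centre = Φ((d√30 − 1.96) / √(1 − ρ)).
- Power with centre = Φ(d√30 / √(1 − ρ) − 1.96).

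Worked at ρ = 0.15, where √0.85 = 0.922:

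- SE ratio: 1 / 0.922 = 1.085.
- Type I error: 1.96 / 0.922 = 2.126, giving 3.4%.
- Power at 0.60 without centre: (3.286 − 1.96) / 0.922 = 1.439, giving 92.5%.
- Power at 0.60 with centre: 3.286 / 0.922 − 1.96 = 1.604, giving 94.6%.

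| ρ | SE overstated | Type I error | Power at 0.60, without / with centre | Forgone | Power at 0.40, without / with centre | Forgone |
|---|---|---|---|---|---|---|
| 0 | 0% | 5.0% | 90.8 / 90.8% | 0 | 59.1 / 59.1% | 0 |
| 2% | 1.0% | 4.8% | 91.0 / 91.3% | 0.3 | 59.2 / 60.0% | 0.8 |
| 5% | 2.6% | 4.4% | 91.3 / 92.1% | 0.8 | 59.4 / 61.3% | 2.0 |
| 10% | 5.4% | 3.9% | 91.9 / 93.4% | 1.5 | 59.6 / 63.7% | 4.0 |
| 15% | 8.5% | 3.4% | 92.5 / 94.6% | 2.1 | 59.9 / 66.1% | 6.3 |

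Forgone power is in percentage points, taken before rounding. Power without centre does not fall as ρ rises, because total variance is held fixed and stratification removes the centre part from the estimate itself.

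**Simulation check.** ANCOVA at week 12, five centres, 12 per arm per centre, assumed baseline correlation 0.4, 4,000 runs per setting. At ρ = 0.10 the mean SE without and with centre was 0.166 and 0.159, type I error 4.1% and 4.9%, and power at 0.40 67.1% and 70.7%. At ρ = 0.20, outside the range above, the figures were 0.164 and 0.150, 3.5% and 5.1%, and 68.7% and 75.2%. Powers exceed the table's because baseline adjustment reduces the residual variance. The direction agrees. The SE ratio at ρ = 0.10 (0.1658 / 0.1589 = 1.043) is below the formula's 1.054, because the realised spread of only five centres averages four-fifths of the nominal variance: √[(0.90 + 0.8 × 0.10) / 0.90] = 1.043.

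**The case against.** **This belongs in the statistical analysis plan.** Only the protocol is at hand, design covariates are often settled later, and a list that says what the fixed effects will include is not strictly closed. This softens the point but does not remove it. The protocol does not defer the model: it sets out the fixed effects, the random effect, the contrast and the alpha level, without the factor used to randomise.

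**The loss is not established.** A reader might infer that the standard error is too large as a matter of fact and that power is certainly lost. The documents do not support that. Both depend on between-centre variance remaining after baseline MADRS, which the protocol never gives. Central training, checklists, written procedures and inter-rater exercises are all meant to keep it small. At ρ = 0 nothing is lost. This part of the objection stands, and the point is therefore conditional.

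**The trial is not underpowered by this.** A reader might also infer that the planned power fails. It does not: the model without centre stays above 90% at 0.60 throughout the range. The larger figures arise only at 0.40, which the protocol cites as a clinical-utility threshold for monotherapy and not as its powering assumption.

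**The formula is a best case.** It assumes exact balance within centre among completers and charges nothing for the extra degrees of freedom. A simulation with 150 randomised, assumed blocks of four within centre and two severity levels, and 20% random dropout gave an SE excess of roughly 1 to 4% at ρ = 0.05. The power gain at 0.60 was about 1 point there and about 1.5 points at ρ = 0.10. With no centre variance, adding centre cost up to about 0.5 point. The effect stays small and its direction holds.

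**The severity stratum.** It is tempting to say this factor is missing too. The randomisation section does not name the severity scale. The Screening section uses HRSD-24 for severity, but nothing says that the stratum is built from it. Baseline MADRS is in the model and broadly covers severity.

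**Conclusion.** The point holds in conditional form. The protocol randomises by centre and states a primary model with centre as neither a fixed nor a random effect. If centres differ in week-12 MADRS after baseline adjustment, the reported standard error will be somewhat too large, the interval too wide and the test conservative.

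Over an assumed residual centre share of 0 to 15%, the overstatement is 0 to about 8.5%, type I error falls from 5% to about 3.4%, and the power forgone is 0 to about 2 points at 0.60 and 0 to about 6 points at 0.40. These figures rest on the assumed share, on balance within centre among those followed up, and on a centre difference at week 12 that a single centre term captures.

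Omitting centre does not by itself bias the estimate, does not inflate type I error, and does not endanger the 90% power at 0.60. It is an inexpensive improvement, not a flaw that invalidates the analysis.

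**What to change.** In the Statistical Analysis section, add study centre to the fixed effects of the primary mixed model, and state that the secondary mixed models carry the same term. Name the scale and cut that define the severity stratum, and add the stratum as a fixed effect only if it is not a cut of baseline MADRS. Make the change before unblinding so that it is prespecified.

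The cost is a line of wording and 4 degrees of freedom if there are five centres (5 − 1). No change to sample size, visits or data collection is needed. If centres turn out not to differ, the price is at most about half a point of power.

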#### *Follow-up*

Participants will continue with the treatment currently provided by their clinical teams. Simvastatin will be started at a dose of 20mg daily. Assessments will be at baseline, weeks 2, 4, 8 and 12.

The clinical team and consultant psychiatrist will continue to oversee routine care for each participant although research assistants will be contactable for the duration of the study to respond to any concerns. Demographic data will be collected by RAs at baseline and will include age, gender, marital status, socio-economic status, highest level of education, smoking status, and concomitant medication.

Participants will be asked to bring all leftover medications to each follow up visit, so that RAs can complete a pill count to monitor compliance. On each visit the research assistant will meet with patient at an agreed location to complete the follow up assessment.

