**Table 1: Assessment Schedule**

| Assessment                                  | Baseline | Week 2 | Week 4 | Week 8 | Week 12 | Ad hoc |
|---------------------------------------------|----------|--------|--------|--------|---------|--------|
| Medical Confirmation of Eligibility, SCID-5 | ✓        |        |        |        |         |        |
| Randomisation                               | ✓        |        |        |        |         |        |
| MADRS                                       | ✓        | ✓      | ✓      | ✓      | ✓       |        |
| HRSD-24                                     | ✓        | ✓      | ✓      | ✓      | ✓       |        |
| CGI                                         | ✓        | ✓      | ✓      | ✓      | ✓       |        |
| GAD-7                                       | ✓        | ✓      | ✓      | ✓      | ✓       |        |
| MMAS-4                                      | ✓        | ✓      | ✓      | ✓      | ✓       |        |
| Simvastatin dispensed                       | ✓        | ✓      | ✓      | ✓      | ✓       |        |
| TAU/Concomitant medication                  | ✓        | ✓      | ✓      | ✓      | ✓       |        |
| Adverse Effects Scale                       |          | ✓      | ✓      | ✓      | ✓       | ✓      |
| Basic clinical & psychiatric information    | ✓        |        |        |        |         |        |
| BMI                                         | ✓        | ✓      | ✓      | ✓      | ✓       |        |
| Biomarkers (CRP, lipids)                    | ✓        |        | ✓      |        | ✓       |        |

|                   |  |  |  |  |  |   |
|-------------------|--|--|--|--|--|---|
| Telephone contact |  |  |  |  |  | ✓ |
|-------------------|--|--|--|--|--|---|

613  
614  
615  
616  
617

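### When adverse events are few, the fallback fits a separate count model at each of four visits, which splits sparse data further and gives no overall 12-week comparison of adverse-event rates

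*Protocol*

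**What the plan says.** All of this is in the protocol; no SAP was available.

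- **Aim and main method** (Statistical Analysis). After descriptive summaries by group: "Differences in the rates of AEs will be assessed by generalized linear mixed" models, with time, treatment group and their interaction as fixed effects and subjects as random effects.
- **Condition** (same sentence). The "model with Poission or negative binomial distribution will be used given sufficient numbers" of events.
- **Fallback** (next sentence). "Alternatively, simple count models will be used at each timepoint given the" "limited sample size and complexity of GLMM models".
- **Timepoints.** Under Follow-up, "Assessments will be at baseline, weeks 2", 4, 8 and 12. Table 1 schedules the "Adverse Effects Scale" at weeks 2, 4, 8 and 12 and also ad hoc, so the fallback has four scheduled timepoints.
- **Error rate.** "Two tailed tests and an alpha level of 0.05 will be used for significance". The paragraph before the adverse-event text, on secondary efficacy outcomes, adds "comparisons using a correction based on controlling the family-wise error" and calls timepoints other than week 12 exploratory. Neither statement is tied to adverse events, and neither excludes them.

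The protocol states no expected adverse-event rate, no power for adverse events, and no pooled comparison for use when the mixed model is abandoned.

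**The concern.** The fallback answers its own trigger the wrong way round. If events are too few to support a model across visits, dividing them among four visits leaves each model with less information still. The question was whether adverse-event rates differ between arms. The four models address four visit-specific questions, and no step combines them into a 12-week rate ratio with a confidence interval. Ad hoc reports have no stated place in any of the four.

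At stake is the only inferential safety comparison in the plan, in the case of low counts among 150 participants, which is plausible. Non-significant results at individual visits could be read as reassurance that the data cannot give. A single significant visit could be read as a signal with no agreed error rate behind it.

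**Working it through.** **Design figures.** The protocol gives no adverse-event figure to reproduce. Its efficacy sample size, which supplies the numbers per arm, does reproduce: effect size 0.60, two-sided 5% and 60 per arm give 90.3% power by t-test, and 120 / (1 − 0.20) = 150 randomised, or 75 per arm.

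**Assumptions not in the protocol.** Adverse-event rates (a range is shown), a doubled rate as the real harm, and gamma frailty variance 0.5 to 1.0 for differences between patients.

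**Step 1: why splitting costs power.** For Poisson totals x (control) and y (simvastatin) in equal arms, SE(log rate ratio) ≈ √(1/x + 1/y). Take 5 control events per visit and a rate ratio of 2, so ln 2 = 0.693:

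- One visit: √(1/5 + 1/10) = 0.548; 0.693 / 0.548 = 1.27; power ≈ Φ(1.27 − 1.96) ≈ 24%.
- Four visits pooled: √(1/20 + 1/40) = 0.274; 0.693 / 0.274 = 2.53; power ≈ Φ(2.53 − 1.96) ≈ 72%.

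**Step 2: exact enumeration.** Power is the sum of P(x)P(y) over all (x, y) for which the test rejects at 5%. Ranges cover the score, Wald, likelihood-ratio and exact tests. There is no clustering within patients.

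| Control events per visit (12-week total) | Power, single visit | Power, pooled |
|---|---|---|
| 2 (8) | 2–18% | 30–39% |
| 5 (20) | 18–27% | 70–75% |
| 10 (40) | 37–46% | 95–96% |

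At 15 control events per visit a single visit reaches 56–62%. A single visit therefore misses a doubling more often than not up to about 10 control events per visit, but no longer does at 15.

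**Step 3: simulation with clustering and dropout.** 75 per arm, 20% dropout, frailty variance 0.5 to 1.0, visit intervals of 2, 2, 4 and 4 weeks, robust Wald tests, rate ratio 2. Before dropout, 0.2 events per placebo patient is 75 × 0.2 = 15 control events over 12 weeks, and 0.5 is 75 × 0.5 = 37.5.

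| | 0.2 per placebo patient | 0.5 per placebo patient |
|---|---|---|
| Power, average single visit | about 9% | about 32–33% |
| Power, any of four, unadjusted | 29–32% | 74–78% |
| Power, four tests with Bonferroni | not tabulated | 42–44% |
| Power, one pooled test | 44–50% | 74–83% |
| False signal at some visit, unadjusted, no true difference | 0–3% (covers 0.1–0.2) | about 14–15% |

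**Step 4: false signals from four tests.**

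- Four independent, calibrated, unadjusted tests: 1 − (1 − 0.05)⁴ = 1 − 0.8145 = 18.5%.
- Correlation between visits of 0.3, 0.5 and 0.7: 17.4%, 15.6% and 13.0%.
- Very sparse counts (2 events per arm per visit): 0.2% (Wald), 2.0% (exact), 15.5% (score), 33.5% (likelihood ratio).
- Bonferroni at 0.05 / 4 = 0.0125: at most 1 − (1 − 0.0125)⁴ = 4.9%, at the cost in power shown in step 3.

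**Step 5: variance in the pooled test.** With frailty variance 1 and no true difference, a plain pooled Poisson likelihood-ratio test rejected in 8–29% of trials across the rates tried. A robust one stayed at about 5%. Pooling therefore needs a negative binomial or robust variance.

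**The case against.** **A fixed false-signal multiple.** A reader might infer that the four tests give false signals at about three times 5%. The protocol does not support that. It names no test, and in the sparse case that triggers the fallback the rate runs from near 0 to over 30%, depending on the test. It also does not say that adverse-event tests go unadjusted. This part of the objection stands, so no single multiple is claimed here. If the family-wise correction does apply, false signals are controlled but power falls further.

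**A doubling would be missed altogether.** A reader might also infer that a real doubling would usually pass as no safety difference. At 0.5 events per placebo patient, four unadjusted tests flag it at some visit in 74–78% of trials, close to pooling. That stands too, but it comes with the false-signal rate of about 14–15%. At 0.2 per patient, pooling is clearly better even than any of four. Descriptive summaries by group, 95% intervals and a DSMB with unblinded data would also make a doubled count visible. This limits the harm without supplying the missing comparison.

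**Lost random effect.** A model for one visit has one count per participant, so losing the subject effect is no defect in itself. Overdispersion is handled if simple count models include the negative binomial, which the preceding sentence names.

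**Visit-specific effects are already the plan.** The mixed model has a treatment-by-time interaction. True, but a model fitted to all visits can still yield an overall contrast; four separate models have no step that does.

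**Summing may double-count.** The events come from a scale completed at each visit, with no recall window stated. A persisting symptom could be counted several times. This stands, and the fix needs a counting rule.

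**It belongs in the SAP.** The test and the multiplicity rule may well be there. The choice to split by visit when data are sparse is already fixed in the protocol.

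**Conclusion.** The point holds in a limited form. When events are few or the mixed model is too complex, the stated fallback divides sparse data by four and never estimates the 12-week difference in adverse-event rates. Under the stated assumptions, pooling raises power for a doubled rate from 29–32% (any of four, unadjusted) to 44–50% at 0.2 events per placebo patient. At 0.5 per patient it gives 74–83%, against 42–44% for four tests with the family error held at 5%. All power figures rest on assumed event rates, because the protocol states none. The false-signal rate cannot be given as one number: it is up to 18.5% for four calibrated, independent, unadjusted tests, about 13–17% at correlations of 0.3 to 0.7, and test-dependent when counts are very sparse. The choice should be changed. It does not affect the primary efficacy analysis.

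**What to change.** Replace the fallback sentence with:

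> If the GLMM is not supported, each participant's new (onset) adverse events will be summed over follow-up, a continuing event being counted once, and compared between arms in one negative binomial or robust-variance Poisson model with log follow-up time as offset. The rate ratio and 95% CI will be reported. Counts by visit will be descriptive only.

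This costs one sentence of wording and no extra visits or measurements, provided the records let a new event be told from a continuing one. Ad hoc reports then have a place in the count, and participants who leave early contribute their time under observation. The downsides are small: differences at individual visits are described and not tested, and very sparse events will still leave low power (44–50% for a doubling at 0.2 events per placebo patient), so the interval should be read before the p value.
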